### Magnetic resonance imaging

Cardiovascular MRI is considered the most accurate measure to date for evaluation of LVEF, the extent of myocardial infarct size, and several other functional parameters [36]. The diagnostic accuracy of MRI for evaluation of LVEF allows a sample size reduction compared to other imaging modalities. Patients are studied with a 3.0 Tesla clinical scanner (3 T Achieva, Philips, Best, The Netherlands) at the NeuroImaging Center (NIC, University of Groningen, Groningen, The Netherlands) (Appendix C) using a phased array cardiac receiver coil. Electrocardiogram-gated cine steady-state, free precession magnetic resonance images acquired during repeated breath holds in the standard long-axis views (4-, 3-, and 2-chamber view) and contiguous short-axis slices covering the entire left ventricle are used to assess global and regional ventricular function and to calculate LVEF (primary endpoint). Using identical slice locations, late contrast-enhanced (LCE) images are acquired 10 min after intravenous administration of a gadolinium-based contrast agent (Dotarem, Gorinchem, the Netherlands; 0.2 mmol/kg) with an inversion-recovery, gradient-echo pulse sequence to identify the location and extent of MI. The inversion time will be set to null the signal of viable myocardium for every individual patient. All MRI data are sent to independent cardiologists, blinded for randomization status, for quality control and blinded analysis (Appendix D).

The MRI data are analyzed using a dedicated software package. On the stack of short-axis cines, the endocardial and epicardial borders are outlined in end systolic and end diastolic images. Left ventricular end diastolic volume (LVEDV) and left ventricular end systolic volume (LVESV) are calculated using the summation of slice method multiplied by slice distance. LVEF is calculated as LVEF = 100 % × (LVEDV-LVESV)/LVEDV. Summation of the volumes per slice of areas of hyperenhancement is outlined, allowing to calculate total infarct size.

### Echocardiography

Two-dimensional echocardiography with a phased array electronic ultrasound will be performed 0–2 days after randomization and 4 months after randomization. Tissue Doppler (TD) imaging of the early mitral valve flow velocity/early TD lengthening velocity (*E/E’)*, the ratio of the early (E) to late (A) mitral valve flow velocity, the deceleration time, the left atrial volume index (LAVI), and the difference between the duration of reverse pulmonary vein atrial systole flow (Ard) and mitral valve atrial wave flow (Ad) will be used to determine and classify diastolic function.

### Skin autofluorescence

Tissue AGE accumulation will be assessed using a validated skin autofluorescence (AF) reader (advanced glycation endproducts reader; patent PCT/NL99/00607; DiagnOptics BV, Groningen, The Netherlands) [38]. In short, a skin surface of approximately 2 cm^2^ is illuminated by the AGE-reader with an peak excitation of ~370 nm. The reflected light from the skin is measured with a spectrometer in the 420–600 nm range, using 200 μm glass fibers. The value of skin AF is calculated as the ratio of the light intensity in the 420–600 nm wavelength range and the light intensity in the 300–420 nm wavelength range. Skin AF will be measured during hospitalization, and 4 months after randomization.

### Electrocardiography

A standard 12-lead electrocardiogram is acquired at the time of presentation, after the PCI procedure, before hospital discharge, and at each outpatient clinic visit. Mean time interval between pre and post intervention will be registered. Pre-intervention ECG will be analyzed on the presence of ST-deviation. The post-intervention ECGs will be used to score persistent ST-deviation and ST-segment resolution, and the incidence and location of new Q-waves.

### Laboratory analysis

During hospitalization, blood will be sampled at baseline and at 3, 6, 9, 12, and 24 h after PCI to monitor values of cardiac enzymes and high sensitive troponin [39]. Less frequently during hospitalization and at every visit to the outpatient clinic hemoglobin, platelets, glucose, creatinin and liver enzymes, total cholesterol, high-density and low-density lipoprotein, and N-terminal pro B-type natriuretic peptide will be determined.

Furthermore, during PCI, 24 h after PCI, and at every visit to the outpatient clinic, blood samples for additional analyses will be collected [40]. These analyses will include, but are not limited to, glycometabolic determinants, biomarkers, and other markers of disease severity or relevant to the disease [41, 42].

### Diabetes and prediabetes

For assessment of diabetes and prediabetes, an oral glucose tolerance test (OGTT) will be performed during initial hospitalization and after study medication is stopped according to protocol and after primary endpoint analysis, next to the level of glycated hemoglobin (HbA1c) [40]. Diabetes and prediabetes will be diagnosed according to current guidelines [43]. Whenever new onset diabetes is diagnosed, patients will be treated by an endocrinologist according to current guidelines, additional to study treatment. Metformin can be started on top of study medication in a dose of 500 mg three times per day, to prevent exceeding maximal metformin dose. Patients who next to standard care and life style interventions need oral antihyperglycemic agents or insulin for glucose control prior to primary endpoint analysis will be excluded from the per protocol analysis.

## Statistical considerations

### Sample size

The sample size is calculated for the difference in the primary efficacy parameter (LVEF measured by MRI at 4 months) between the intervention group and the placebo group. With 80 % power to detect a 3 % difference in LVEF between active treatment and control (assuming a 2-sided α of 0.05 and an SD of 9 % for the change in LVEF) 141 patients are needed in each study group. A 3 % difference in LVEF is considered to be a clinically relevant outcome [37]. Based on local experience from previous studies, we assume that MRI analysis will be unavailable in up to 24 % of patients (due to study withdrawal, development of contraindications e.g. ICD, claustrophobia, etc.) [44, 45]. To maintain 80 % power, an increase to a total of 350 patients is required. However, if actual study completion rates differ from predicted rates, recruitment will be extended in order to achieve 282 patients with primary endpoint analysis. The maximal number of patients to which the inclusion can be extended in this trial will be limited to 380.

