**Methods:**

The Glycometabolic Intervention as adjunct to Primary percutaneous intervention in ST elevation myocardial infarction (GIPS)-III trial is a prospective, single center, double blind, randomized, placebo-controlled trial. Three-hundred-and-fifty patients, without diabetes, requiring primary percutaneous coronary intervention (PCI) for STEMI will be randomized to metformin 500 mg twice daily or placebo treatment and will undergo magnetic resonance imaging (MRI) after 4 months. Major exclusion criteria were prior myocardial infarction and severe renal dysfunction. The primary efficacy parameter is left ventricular ejection fraction 4 months after randomization. Secondary and tertiary efficacy parameters include major adverse cardiac events, new onset diabetes and glycometabolic parameters, and echocardiographic diastolic function. Safety parameters include renal function deterioration and lactic acidosis.

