### Study efficacy parameters

The primary efficacy parameter of the GIPS-III trial is LVEF measured by cardiac MRI 4 months after randomization, based on an intention-to-treat analysis. LVEF, is an important predictor of prognosis after MI [36, 37].

A per-protocol analysis, excluding patients diagnosed with new onset diabetes and treated with oral antihyperglyceemic agents or insulin prior to cardiac MRI, will be performed as a secondary efficacy parameter. Other secondary efficacy parameters include major cardiac adverse events (MACE; death, recurrent MI, target lesion revascularization), stroke, non-elective hospitalizations for chest pain or heart failure, all recurrent coronary interventions, and internal cardiac defibrillator implantations. Mortality will be divided into cardiac and non-cardiac. Cardiac death will be divided into three categories: heart failure, sudden death and other. A cardiologist will confirm deaths from cardiovascular causes by examining medical records obtained from hospitals and attending physicians or from the attending general practitioner if the patient died at home. Further, echocardiographic parameters of diastolic function, incidence of new onset diabetes, additional parameters measured by MRI, skin autofluorescence, electrocardiographic parameters, and blood sample analyses, will be used as tertiary efficacy endpoints.

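### The sample size is set for 4-month LVEF but uses an SD labelled as that of the change in LVEF, so the stated 80 % power is not supported for the variable analysed

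*Protocol article*

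**What the plan says.** The Sample size section opens by naming the variable: "The sample size is calculated for the difference in the primary efficacy parameter (LVEF measured by MRI at 4 months"), compared between the metformin and placebo groups. The next sentence gives the target, "With 80 % power to detect a 3 % difference in LVEF", and then the variability, an SD of 9 % "for the change in LVEF) 141 patients are needed in each study group", or 282 evaluable patients in all.

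Study efficacy parameters defines the endpoint in the same way as that opening: "The primary efficacy parameter of the GIPS-III trial is LVEF measured by cardiac MRI 4 months after randomization, based on an intention-to-treat analysis". The abstract says that patients "will undergo magnetic resonance imaging (MRI) after 4 months" and mentions no earlier scan. The Magnetic resonance imaging section describes how scans are acquired and read, and it too mentions no baseline scan. The only early cardiac imaging described is echocardiography at 0–2 days, used to classify diastolic function. For continuous outcomes the statistical section names an independent-samples t test or a Mann–Whitney U test, with no change score and no baseline term.

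**The concern.** A 4-month value and a change from baseline are different variables and in general have different SDs. Within one paragraph the article names the first as the quantity to be compared and takes the SD of the second. The power of a two-sample comparison depends on the SD of the variable that is compared, so the stated 80 % carries over only if the two SDs happen to agree.

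At stake is how the result will be read. The Discussion calls this a proof-of-principle trial, and the weight of a null result depends on the real power for 3 points. The plan's safeguard does not cover the problem. Recruitment is extended only if completion rates differ from those predicted, and always towards the same 282 evaluable patients, so an SD other than 9 would trigger nothing.

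**Working it through.** **Inputs (Sample size section).** Difference δ = 3 LVEF points; SD = 9; two-sided α = 0.05; power 80 %; equal groups.

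**Step 1: reproduce the stated figure.** Normal approximation:

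n per group = 2 × [SD × (1.960 + 0.842) / δ]² = 2 × [9 × 2.802 / 3]² = 141.3

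Power at 141 per group is 79.9 % by this approximation and 79.7 % by the t test. The stated 141 is therefore reproduced, with 9 entered directly as the SD of the compared variable.

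**Step 2: what if the SD of 4-month LVEF is not 9?** The article gives no such SD, so a range is assumed (t test, 141 per group, δ = 3):

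| Assumed SD of 4-month LVEF | Power |
|---|---|
| 8 | 88 % |
| 9 | 80 % |
| 10 | 71 % |
| 11 | 63 % |
| 12 | 55 % |

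**Step 3: what if 9 really is the SD of a change?** With correlation r between baseline and 4 months,

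Var(change) = SD₀² + SD₄² − 2r·SD₀·SD₄

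Assume SD₀ = SD₄. Then Var(change) = 2·SD₄²(1 − r), so SD₄ = 9 / √[2(1 − r)]:

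| r (assumed) | SD₄ | Power at 141 per group | n per group for 80 % |
|---|---|---|---|
| 0.4 | 8.2 | 86 % | 118.7 |
| 0.5 | 9.0 | 80 % | 142.2 |
| 0.6 | 10.1 | 70 % | 177.6 |
| 0.7 | 11.6 | 58 % | 236.4 |

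Power and n are from the t test; n is unrounded.

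**Step 4: how far does Step 3 depend on equal variances?** Setting Var(change) = SD₄² gives SD₀ = 2r·SD₄, so the break-even correlation is r = SD₀ / (2·SD₄). It is 0.5 only when the two SDs are equal. Example: with SD₀ = 1.4 × SD₄ the break-even is 0.7. At r = 0.6, Var(change) = (1.96 + 1 − 1.68) × SD₄² = 1.28 × SD₄², so SD₄ = 9 / √1.28 = 7.95 and power is about 88 %, higher than stated, although r exceeds 0.5.

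**Step 5: can the extension rule absorb a larger SD?** At the cap of 380 randomized and 24 % without MRI, 380 × 0.76 = 288.8 are evaluable, about 144 per group. At SD 10 that gives about 72 % power.

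**The case against.** The strongest reply is that the reference to a change is loose wording. The paragraph opens by saying that the calculation is for 4-month LVEF, and the 9 is used as a plain two-sample SD. If the 9 was meant as the SD of the 4-month value, power is about 80 % as stated and the error is one phrase. This stands as a possibility, but nothing in the article confirms it. The 3 % difference and the 24 % missing rate each carry a citation; the 9 % carries none.

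A reader might infer that the trial is underpowered. The documents do not support that. They give no SD for 4-month LVEF, no baseline-to-follow-up correlation and no ratio of variances, and Steps 3 and 4 show power above 80 % under some assumptions and below it under others. Nor can one say in general that any correlation above 0.5 costs power; that needs equal variances.

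A reader might also infer an arithmetic error. There is none: the figure reproduces, and the defect lies in the input or its label.

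Finally, the absence of a baseline MRI is read from the text, because the flow chart is not shown. That caveat is fair but changes little: even with a baseline scan, neither the endpoint definition nor the named tests use a change.

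**Conclusion.** The point holds as a mismatch between the variable that is analysed and the SD that is used for it. Either the SD belongs to a different variable or it is mislabelled; on both readings the paragraph is wrong as written and the 80 % is unsupported. That the SD of 4-month LVEF is undocumented is certain. That power is lost is not shown.

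The size is conditional. At 141 per group, power runs from 88 % to 55 % for assumed 4-month SDs of 8 to 12. If 9 is a change SD with equal variances, it runs from 86 % to 58 % for r from 0.4 to 0.7. These are illustrations and not estimates.

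**What to change.** State the SD of 4-month MRI LVEF and its source, and restate the power that 282 evaluable patients give for a 3-point difference at that SD. One source is the trial itself: the pooled SD, blinded to arm, of the 4-month MRIs available. The article reports 266 patients randomized by August 2012 with recruitment still open, though it does not say how many scans had been read. A pooled SD of this kind includes any treatment effect, but only slightly: with a true SD of 9, a true difference of 3 and equal groups it would be √(81 + 3²/4) = 9.1.

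If 9 % is already the SD of a 4-month value, delete the words that tie it to a change and cite where it comes from.

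The cost is a blinded calculation or a citation, and a reworded sentence. The stated power may become less favourable. Restating it needs no unblinding, spends no α and requires no added patients.

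### At the 24% upper bound for missing MRI, and before any extension, 350 patients give 266 evaluable scans and about 77% power; 372 are needed for 282

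*Protocol article*

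**What the plan says.** All the relevant statements are in the protocol article, Statistical considerations, Sample size.

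- Design target: "With 80 % power to detect a 3 % difference in LVEF between active treatment and control". The calculation uses a two-sided 5% level and takes the standard deviation of LVEF change to be 9 points.
- Evaluable number: "141 patients are needed in each study group", which is 282 in total.
- Loss allowance: "we assume that MRI analysis will be unavailable in up to 24 % of patients".
- Inflated total: "To maintain 80 % power, an increase to a total of 350 patients is required".
- Extension: "if actual study completion rates differ from predicted rates, recruitment will be extended in order to achieve 282 patients with primary endpoint analysis", with an upper limit of 380 patients.

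The total of 350 is repeated as the trial size in the Abstract (Methods), in Study design and in the Conclusion.

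**The concern.** The loss is expressed as a share of the patients enrolled, so the evaluable number is the enrolled number times 0.76, and the enrolled number is found by dividing 282 by 0.76. The printed total is instead what results from adding 24% of 282 to 282. Adding a percentage of the evaluable number always gives too small a total, because the loss applies to the larger enrolled number.

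What is at stake is the design power for the primary endpoint. A total that is justified by an upper bound on loss should hold at that bound, and 350 does not. The allowance actually built into 350 is about 19%, not 24%. Anyone who checks the section will find that its central figure does not reproduce from its own inputs.

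**Working it through.** **Inputs, all from the Sample size section.** Difference 3 points; SD 9, taken as printed; two-sided alpha 0.05; power 80%; 141 per group, 282 in total; MRI loss up to 24%; stated total 350; cap 380. Equal allocation is assumed, in line with the single per-group figure.

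**1. Reproduce the evaluable number.**
Normal approximation: n per group = 2 × (1.960 + 0.842)² × 9² / 3² = 2 × 7.85 × 9 ≈ 141.3. The stated 141 is this value rounded down. The t-test solution is 142.2. The 141 is therefore accepted, and 282 is used as the plan's own target.

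**2. Reproduce the inflated total.**

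| Calculation | Result |
|---|---|
| 282 × (1 + 0.24) | 349.7, rounded up to 350 (the stated figure) |
| 282 / (1 − 0.24) | 371.05, or 372 with equal groups (141/0.76 = 185.5, so 186 each) |

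Only the multiplication gives the printed 350. This is an inference from the match. The shortfall in step 3 does not depend on it.

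**3. What 350 delivers at 24% loss, before any extension.**
350 × 0.76 = 266 evaluable, or 133 per group. This is 282 − 266 = 16 scans short of target, equivalent to 372 − 350 = 22 enrolled patients.

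**4. Power** for a 3-point difference, SD 9, two-sided alpha 0.05. The normal approximation is Φ(3 / (9 × √(2/n)) − 1.960), with n per group.

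| Enrolled | Loss | Evaluable | Normal approximation | t-test |
|---|---|---|---|---|
| 350 | 24% | 266 | 77.6% | 77.3% |
| 350 | 20% | 280 | 79.6% | 79.4% |
| 350 | 19.4% | 282 | 79.9% | 79.7% |
| 380 (cap) | 24% | 288.8 | 80.9% | 80.6% |

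The drop from 282 to 266 evaluable patients is 79.7 − 77.3 = 2.4 points on the t-test.

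**5. Loss that each total can absorb while keeping 282.**
350: 1 − 282/350 = 19.4%. 
380: 1 − 282/380 = 25.8%.

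The cap therefore has room for the stated 24%; the total of 350 does not.

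**The case against.** Three arguments limit the point.

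*The 24% is a ceiling.* This stands in part. Any loss up to 19.4% still leaves 282 evaluable patients, so the 77% figure belongs to the worst case in the stated range and not to every case. But the text offers 350 as the number that keeps 80% power given that ceiling, and between 19.4% and 24% it falls short.

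*The extension rule already protects the target.* This is the strongest argument, and most of it stands. The rule names its purpose, "recruitment will be extended in order to achieve 282 patients with primary endpoint analysis", and its cap of 380 exceeds the 372 needed. A reader might infer that the trial will stop at 350 with 266 scans if loss is exactly 24%, because nothing would then differ from prediction, and so conclude that the trial is underpowered. The document does not support that conclusion. It is one literal reading of a loosely worded condition. A prediction given as an upper bound has no exact predicted rate to depart from, and a team that expects 350 to produce 282 would probably see a shortfall as a departure from prediction and extend. What remains is ambiguity: the trigger is set against a predicted rate that already leaves 350 short, so the text does not say clearly whether extension applies at that rate.

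*The link from 350 to 282, and the multiplication, are inferred.* This is correct. The section does not say in so many words that 350 patients yield 282 scans, and it shows no inflation formula. The mismatch holds regardless, since 80% power was tied to 282 and 350 × 0.76 is 266.

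**Conclusion.** The stated total is wrong as written. At the plan's own upper bound for missing MRI, and before any extension, 350 patients give 266 evaluable scans and 77.3% power (t-test; 77.6% by normal approximation), not the 80% claimed. The correct total for 282 evaluable patients at 24% loss is 372.

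The practical effect is modest: 16 scans, or about 2.4 points of power, and only for losses above 19.4% that are not made up by extension. Type I error and the planned comparison are unaffected. The extension rule can close the gap within the existing cap, although its trigger needs clearer wording. Severity is minor to moderate.

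The conclusion rests on equal allocation, equal loss in the two groups, and the difference and SD as printed.

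**What to change.** Change two statements in the Sample size section.

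1. Restate the total, for example: *350 patients give 80% power if MRI is missing in up to about 19%, and about 77% power at 24%; 372 patients, within the maximum of 380, are needed for 282 evaluable at 24% loss.* If 372 is adopted as the planned total, change the 350 in the Abstract, Study design and Conclusion to match.
2. Replace the trigger, for example: *if fewer than 282 evaluable MRIs are projected, recruitment will continue until 282 are expected, up to 380 patients.*

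The cap of 380 stays. Restating the figure alone costs only the edit. Planning for 372 adds 22 patients. The Current status section reports 266 patients randomised from January 2011 to 1 August 2012 (a count of enrolled patients that happens to equal the evaluable figure above). Over about 19 months that is 14 per month, so 22/14 ≈ 1.6 months of extra recruitment. The same section describes enrolment as still open at that date, so on the text shown both changes could be made before it closed.

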### Statistical analyses of primary and secondary efficacy parameters

The primary efficacy parameter of the study is measured 4 months after randomization. For the analysis of binary endpoints, treatment comparisons will be performed using Fisher exact probability test or Chi-square analysis. For continuous outcomes, independent samples *t* test or a Mann–Whitney *U* test will be used, as appropriate. For clinical outcomes such as the incidence of major adverse cardiac events, Cox regression will be used to evaluate the association between the intervention and the endpoints. Kaplan-Meier curves displaying the pattern of events over the 4-month and long-term follow-up period will be drawn.

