**Fig. 3 Fig3:**
[figure not shown]
Flow chart of the GIPS-III trial. STEMI, ST-elevation myocardial infarction; PCI, percutaneous coronary intervention; LVEF, left ventricular ejection fraction; MRI magnetic resonance imaging; OGTT oral glucose tolerance testing

Subjects are scheduled for return visits at 2 weeks, 2 months, 4 months, and 12 months after hospital discharge. During every visit examination, assessment of clinical events and 12-lead electrocardiography are performed. During the 4 month visit the amount of study drug received, dispensed, and consumed will be recorded.

Study drug treatment will be discontinued in the following situations: 1) when subject withdraw consent, 2) in case of pregnancy, 3) when subjects develop severe renal dysfunction (defined as creatinin >177 μmol/L, or an estimated GFR <30 ml/min*1.73 m^2^), or 4) when subjects develop a condition which, in the investigator’s judgment, precludes further therapy. Discontinuation will have no consequence for the regular patient care. Since metformin therapy used as a single antihyperglycemic drug is not associated with hypoglycemia and due to the blinded nature of this trial, there will be no dose modifications of the study medication.

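### Blood markers with a pre-randomisation sample would be compared more precisely by adjusting for that sample than by the unadjusted two-sample test, the only method the article names for continuous outcomes (minor; exploratory endpoints only)

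*Protocol article*

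**What the plan says.** The statistical section of the protocol article, headed "Statistical analyses of primary and secondary efficacy parameters", states: "For continuous outcomes, independent samples *t* test or a Mann–Whitney *U* test will be used, as appropriate". It names no covariate, no repeated-measures model and no key time point for laboratory markers.

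The section Study efficacy parameters ranks the blood markers as tertiary: "skin autofluorescence, electrocardiographic parameters, and blood sample analyses, will be used as tertiary efficacy endpoints". The abstract lists glycometabolic parameters among the secondary and tertiary parameters without separating the two ranks.

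The section Laboratory analysis describes three sampling streams:

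- Cardiac enzymes and troponin: "During hospitalization, blood will be sampled at baseline and at 3, 6, 9, 12, and 24 h after PCI".
- Routine markers: "Less frequently during hospitalization and at every visit to the outpatient clinic hemoglobin, platelets, glucose, creatinin and liver enzymes". Lipids and natriuretic peptide belong to the same list.
- Additional analyses, including glycometabolic determinants and biomarkers: "during PCI, 24 h after PCI, and at every visit to the outpatient clinic, blood samples for additional analyses will be collected".

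The visits are set out in the Treatment section: "Subjects are scheduled for return visits at 2 weeks, 2 months, 4 months, and 12 months after hospital discharge". The same section places randomisation after successful PCI and within 3 hours of it, so a sample drawn during PCI precedes randomisation. Table 2 adds that creatinine is measured before PCI as an exclusion criterion.

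**The concern.** A two-sample t or Mann-Whitney test on the follow-up value takes one number per patient and leaves all between-patient spread in the error term. Where the same marker was measured in the same patient before randomisation, part of that spread is predictable and can be removed at almost no cost. The Discussion promises extensive secondary analyses of mechanism, and these rest largely on such markers. What is at stake is the precision of those answers. The validity of the comparison and the primary LVEF result, for which the article describes no baseline MRI, are not at stake.

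**Working it through.** **1. The plan's own figure.** The only sample size stated is for LVEF: a 3-point difference, SD 9, two-sided 0.05, 80% power, 141 per group.

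n per arm = 2 × SD² × (1.960 + 0.842)² / difference² = 2 × 81 × 7.85 / 9 = 141.3

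This is 141 rounded to the nearest integer, or 142 rounded up. Power at 141 per arm is 79.9%. The figure reproduces. It has no bearing on the blood markers, for which no sample size or effect is stated.

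**2. Which markers have a usable baseline.**

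| Marker group | Value before randomisation stated? | Repeated at outpatient visits? |
|---|---|---|
| Additional samples (glycometabolic determinants, biomarkers) | Yes, during PCI | Yes, all four |
| Creatinine | Yes, pre-PCI (Table 2) | Yes |
| Cardiac enzymes, troponin | A baseline sample is stated | Not listed |
| Glucose, lipids, natriuretic peptide in the routine panel | Not stated | Yes |

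The point applies to the first two rows.

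**3. Variance removed by adjustment.** Let r be the correlation between a marker's pre-randomisation and 4-month values. Adjusted residual variance = (1 − r²) × unadjusted variance. The article gives no r, so 0.3 to 0.7 is an assumption.

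**4. Effect on power.** Further assumptions: 150 per arm with a 4-month sample, a true effect d = 0.25 SD, two-sided 0.05. The noncentrality is d × √(n/2) / √(1 − r²). Unadjusted, this is 0.25 × √75 = 2.165. The powers below use the t distribution.

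| r | 1 − r² | Variance removed | Noncentrality | Power | Equivalent sample-size factor 1/(1 − r²) |
|---|---|---|---|---|---|
| none (unadjusted) | 1 | 0% | 2.165 | 58% | 1 |
| 0.3 | 0.91 | 9% | 2.270 | 62% | 1.10 |
| 0.5 | 0.75 | 25% | 2.500 | 70% | 1.33 |
| 0.7 | 0.51 | 49% | 3.032 | 86% | 1.96 |

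**5. Change scores as an alternative.** A two-sample test on change from baseline has variance factor 2(1 − r): 1.40 at r = 0.3, 1.00 at r = 0.5 and 0.60 at r = 0.7. Adjustment gives 0.91, 0.75 and 0.51. The change score is worse than the raw follow-up value below r = 0.5, and less precise than adjustment at every r in the range.

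**The case against.** The strongest objection is scope. The sentence stands under a heading for primary and secondary parameters, and the blood markers are tertiary. The article nowhere says that they will be tested this way. It also condenses a fuller protocol, and an analysis plan not shown may well specify a model for them. This stands in part: applying the sentence to blood markers is an inference. But the listed secondary parameters are clinical events plus a per-protocol repeat of the LVEF analysis. Read narrowly, the plural continuous outcomes would cover LVEF alone. The comment concerns a method that the article does name, and not a detail that it omits.

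Four stronger readings are tempting, and the text does not support them.

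- *Each patient's starting value is ignored.* The article does not say whether the raw value or the change is compared, and a two-sample test can be run on change. As shown above, that is still less precise than adjustment.
- *Each marker will be tested at every visit.* No such plan is stated. Testing at all four visits at 0.05 would give 1 − 0.95⁴ = 18.5% chance of at least one false positive if the tests were independent, and about 13% (simulated) at an assumed between-visit correlation of 0.7. That describes a practice the wording leaves open, not one it sets out.
- *All repeatedly measured markers have a baseline.* For glucose, lipids and natriuretic peptide in the routine panel, the article states no time before randomisation.
- *The comparison is biased.* Under randomisation the unadjusted test is valid, and its error rate already allows for chance imbalance.

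It is also fair to say that a sample taken during an acute infarction may correlate weakly with one taken 4 months later. That is why r = 0.3, where the gain is small, belongs in the range.

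**Conclusion.** The point holds as a minor improvement. For markers with a value from before randomisation, the one method named gives up precision that adjustment would recover: 9% to 49% of residual variance for r from 0.3 to 0.7. In the worked example that is 58% power against 62% to 86%. The size depends on three assumptions absent from the article: the correlation, the 0.25 SD effect and 150 patients per arm. It also depends on reading the general sentence as covering tertiary endpoints. The loss is one of efficiency in exploratory outcomes. It is not an error in the plan's inference.

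**What to change.** Add a sentence to the section on statistical analyses: continuous markers with a pre-randomisation value are compared at 4 months by a model adjusted for that value, on the log scale where skewed. ANCOVA is enough; a mixed model across visits is an alternative. Name the 4-month contrast as the main comparison for each marker and report the other visits descriptively. The 12-month visit falls about 12 − 4 = 8 months after treatment ends.

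State also that only samples taken before randomisation serve as baseline. This rules out the 24-hour sample and the echocardiogram at 0 to 2 days after randomisation. It also rules out in-hospital skin autofluorescence unless it is shown to precede randomisation. Markers without a pre-randomisation value keep the stated test.

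The cost is wording only, since the samples concerned are already scheduled. The downside is that a model replaces a simple test, and results on the log scale need back-transformation.
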